## Abstract

**Background:**

Respiratory rate (RR) is the most sensitive physiological observation to predict clinical deterioration on hospital wards, and poor clinical monitoring has been highlighted as a primary contributor to avoidable mortality. Patients in intensive care have their RR monitored continuously, but this equipment is rarely available on general hospital wards.

**Objective:**

The primary objective is to assess the accuracy of the RespiraSense device in comparison with other methods currently used in clinical practice. The secondary objective is to assess the accuracy of the RespiraSense device in participants in different positions and when reading aloud.

**Methods:**

A single-center, prospective observational study will investigate the agreement of the RespiraSense device as compared with other device measurements (capnography, electrocardiogram) and the current standard measurement of RR (manual counting by a trained health care professional). The different methods will be employed concurrently on the same participant as part of a single study visit.

**Results:**

Recruitment to this study has not yet started as funding decisions are still pending. Therefore, results are not available at this stage. It is anticipated that the data required could be collected within 2 months of first recruitment to the study and data analysis completed within 6 months of the study start date.

**Conclusions:**

The Evaluation of Agreement of Breathing Rates Measured by a Novel Device, Manual Counting, and Other Techniques Used in Clinical Practice (VENTILATE) study will provide further validation of the use of the RespiraSense device in subjects with abnormal respiratory rates.

**International Registered Report Identifier (IRRID):**

PRR1-10.2196/15437

## Introduction

### Background

Patients admitted to acute hospitals undergo regular monitoring of their vital observations as a key component of their care. In 2007, the National Institute for Health and Clinical Excellence (NICE) produced recommendations for the measurement and recording of physiological observations [1] in response to several multicenter studies that revealed a significant lack of documentation of these observations.

Since the 1990s it has been recognized that the respiratory rate (RR) is the most sensitive physiological observation to predict cardiac arrest on hospital wards [2]. Despite this understanding, monitoring of the RR is demonstrated to be the most common vital sign to be inaccurately measured or recorded [3-5]. More recently, poor clinical monitoring has been highlighted as a primary contributor to avoidable mortality in English hospitals, implicated in 31% of preventable deaths [6].

The most commonly taught and used technique for measuring the RR is manually counting the number of breaths per minute a patient takes. A manual RR should be measured for a period of at least 1 minute, and the normal range for adults (aged 18 years and above) is 12 to 20 breaths per minute [7]. However, a recent cross-sectional study identified significant inaccuracies in the measurement of the RR among UK doctors and highlighted it as an important aspect of clinical care that is currently being poorly performed [8]. Manual counting among other clinical staff in routine practice has also been observed to be inaccurate, possibly due to the approach of counting breaths for 15 seconds and then multiplying by 4 to get breaths per minute, thus introducing error. This leads to somewhat of a self-fulfilling prophecy where expected inaccuracies in the measurement of the RR reduce the confidence of clinical staff at all levels in the usefulness of a reportedly abnormal RR [9].

Patients in intensive care are able to have their RR monitored accurately and continuously by capnography [10]. This type of monitoring can be invasive as it usually requires endotracheal intubation, and patients in other hospital areas do not usually need such an invasive intervention nor is the nursing staff likely to have access to such equipment. However, a systematic review has identified that the existing evidence for routine continuous noninvasive respiratory monitoring on general hospital wards is still inconclusive, and studies are lacking in methodological quality [11]. It recommends that future research should focus on technology explicitly suitable for general hospital wards and explore tailored alarm and treatment algorithms. The first step in such research is to explore the level of agreement between any new technology and current methods of establishing RR.

The significance of the accuracy of the RR recording cannot be overestimated [8,9]; it plays an important role in many clinical assessment systems, including the assessment of acute asthma and systemic inflammatory response syndrome and in the calculation of early warning scores [8]. This score alerts staff to any clinical deterioration and depending on the severity of the score, prompts a review from nursing or clinical staff.

The adoption of these scores has subsequently led to the development of multiple track and trigger information technology systems to allow early detection of patient deterioration [1]. Current systems rely on the manual assessment of the RR by a health care provider (HCP) and entry of data onto a live database in order for it to be processed. At Portsmouth Hospitals NHS Trust (PHT), the Vitalpac (System C) mobile clinical software system is used to record observations and calculates an early warning score (National Early Warning Score [NEWS]) depending on the degree of deviation from the normal range, with the total score proportionate to the overall level of risk (Table 1).

The RespiraSense device (PMD Solutions Ltd) was developed to improve the detection of changes in the RR in order to alert staff to out-of-range values that may be clinically significant. In a 48-patient investigation, data were collected to evaluate the difference in RR measurements between the developed RespiraSense device, electrocardiogram (ECG), and direct nursing observations [12]. A clinically relevant agreement between all RR measurements by the 3 different methods was demonstrated. However, few abnormal values were recorded in this investigation, and further research is required to ensure that the device works well to accurately measure the RR at values both higher and lower than the normal range.

**Table 1 table1:** Escalation protocol for the deteriorating patient [8].

Vital sign	Score						
	3	2	1	0	1	2	3
Pulse	≤40	—	41-50	51-90	91-110	111-130	≥131 Unrecordable due to patient condition
Temperature (°C)	≤35	—	35.1-36	36.1-38	38.1-39	≥39	Unrecordable due to patient condition
BP^a^ systolic (mm Hg)	≤90	91-100	101-110	111-219	—	—	≥220 Unrecordable due to patient condition
Respiratory rate (bpm)	≤8	—	9-11	12-20	—	21-24	≥25 or Unrecordable due to patient condition
AVPU^b^	—	—	—	Alert	—	—	Voice pain unresponsive^c^
SaO_2_^d^	≤91	92-93	94-95	≥96 or Unrecordable because patient refused, equipment unavailable, other reason	—	—	Unrecordable due to patient condition
Inspired O_2_	—	—	—	Air	—	Any supplemental O_2_^e^	—

^a^BP: blood pressure.

^b^AVPU: alert, verbal, pain, unresponsive.

^c^If AVPU is V or C due to patient sedation, it will be charted as S and score 0 rather than 3.

^d^SaO_2_: oxygen saturation.

^e^Note that “any supplemental O_2_” applies to any supplemental oxygen the patient is receiving. It does not apply to patients who are on masks through which only air is being supplied (air delivery possible through tracheostomy, bilevel positive airway pressure or continuous positive airway pressure, for example).

### Objectives

This research aims to assess the accuracy of the RespiraSense device in comparison with other methods (capnography, ECG) and standard care (manual RR monitoring) in healthy participants across a range of predetermined RRs. The information from this study will contribute to the evidence base on RespiraSense to enable its use in clinical practice.

This investigation will supplement the following research that has been conducted in demonstrating the efficacy and/or accuracy of RespiraSense in a clinical setting:

“Evaluation of a continuous monitoring device in capturing respiratory rate compared to industry standard and gold standard” (Bangor, study reference PMD-CS-007)“Can respiratory rate predict the risk of deterioration of septic patients?” (Denmark, study reference PMD-CS-006ii)“A quality assurance study of respiratory rate measurements on obese patients with a novel monitoring technology” (Portsmouth, study reference PMD-CS-011)

The primary objective is to assess the agreement of the RespiraSense device with alternative methods of RR counting in healthy participants. Secondary objectives are to (1) explore whether the position of the participant has any effect on the agreement between the RespiraSense device readings and alternative methods of RR counting, (2) explore whether the agreement of the RespiraSense device and alternative RR methods alters when a participant is reading aloud, and (3) establish agreement between manual counting of the RR and retrospective adjudication of video. The exploratory objective is to record any dermatological effects of the device.

## Methods

### Patient Selection

Selection criteria for the study are shown in Textbox 1.

Selection criteria.
**Inclusion**
Male or femaleAged ≥18 to 60 yearsAble and willing to provide written informed consent
**Exclusion**
Any significant medical condition that may be worsened by the effect of slow or fast breathingSignificant hearing impairmentSkin unsuitable for device following assessment of skin fragilityUnable to access left side of abdominal wall to attach deviceNeuromuscular disease and irregular chest wall movementsAllergy to medical-grade skin adhesivePregnant women during second and third trimester

### Recruitment

Participants will be recruited from the population of staff and students currently working or on placement at PHT. Flyers advertising the study will be posted in communal areas where these groups are likely to congregate (eg, doctors’ mess, ward break rooms). These flyers will contain contact details for the research team and advise those who are interested in taking part in the study to contact the research team.

Potential participants will be contacted by telephone and sent a participant information sheet (PIS). Participants who then wish to take part in the study will be invited to a screening visit. During this visit, the study will be explained, all questions answered, and participant will be screened against the inclusion and exclusion criteria. Additionally, the participant will be asked to breathe at a rate of 30 breaths per minute to assess their comfort while performing a study procedure. Those who are unable to maintain a rate of 30 breaths per minute for 2 minutes will be excluded from the study. Following this screening visit, the participant will be followed up with a telephone call to confirm that they are still willing to take part in the study.

### Study Design

The study is a single-center, prospective observational study to investigate the agreement of the RespiraSense device compared with (1) other device measurements (capnography, ECG) and (2) the current standard measurement of RR (manual counting by a trained HCP). The different methods will be employed concurrently on the same participant as part of a single study visit.

Once participants have provided consent, the following baseline data will be collected:

Demographics (age, sex)Height, weight (to calculate body mass index)Skin assessment at RespiraSense device attachment site (color, texture, uniformity of appearance, integrity). It will also be confirmed that the skin has no discoloration or rash, epidermal loss, blistering, edema, tears, maceration or folliculitisOxygen saturation and pulse oximetry

Participants will be asked to wear a hospital gown and be positioned on an examination couch in the simulation suite. The RespiraSense device, a nasal cannula, and an ECG will be attached and a video recorder positioned to ensure the viewers of the video experience the same image as the HCP performing manual RR monitoring.

A computer-based metronome will be used to produce a repetitive tone at a set rate, which is played to each participant via headphones. The metronome has been produced for the study by the study sponsor team using Microsoft Visual Basic. The metronome rates will be generated using a random number generator program, and the order of the different rates will vary with each participant to ensure the rates are random. The participants will be asked to begin to inspire when each tone is heard and will be given a 20-second warm-up period during which time they will regulate their breathing pattern to match the rate of the tone they hear. Each participant will be asked to breathe at one value from each of the following categories for 2 minutes:

≤8 breaths per minute9 to 11 breaths per minute12 to 20 breaths per minute21 to 24 breaths per minute25 to 29 breaths per minute30 to 35 breaths per minute

One rate will be randomly generated from within each of the 6 categories. Examples of potential sets are shown in Table 2.

**Table 2 table2:** Examples of possible sets of metronome rates to be used.

Participant	First rate	Second rate	Third rate	Fourth rate	Fifth rate	Sixth rate
Participant A	6	10	23	17	28	32
Participant B	5	14	9	22	31	26
Participant C	11	7	13	21	33	27

Each participant will be studied in the normal position (ie, sitting at 45 degrees on a couch) for 6 different metronome rates. They will then be studied in one of the three following additional positions for an additional 4 metronome rates: supine (flat on their back), left lateral decubitus (recovery) position, or sitting at 90 degrees (chair position).

Each metronome rate will be maintained for 2 minutes with 2 to 5 minutes in between for transition (or longer if required by the participant to return to normal breathing rates). A full process flow of the requirements of each participant is shown in Figure 1.

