**Figure 2 figure2:**
[figure not shown]
Schematic of room layout.

Research member 3, blinded to the rates being played in each metronome rate, will record RR values for the continuous ECG and capnography monitoring and the X Series monitor (Zoll Medical Corp) at 60 and 120 seconds. Research member 2 will press the Start and Stop button on the RespiraSense device at the beginning and end of each 2-minute metronome rate and will record the start and stop time on the case report form.

Following the 10 metronome rates, the participant will then be asked to read a verse from a book for 2 minutes. During this time, their RR will be monitored in the same way as for the 10 metronome rates. Once the participant has finished reading aloud, the study will finish.

Throughout the study procedure, a video recording will be made using the portable Scotia Medical Observation and Training System (Scotia UK Plc), the audiovisual system installed in the simulation suite, which includes an in situ camera system (hardware and software).

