Additionally, the randomization of the RRs selected will be prescreened to prevent high variability between tachypnoea and bradypnea in a short space of time. A set of rates will be randomly generated by a custom random number generator which is programmed to select a rate from within each of the categories listed in the Study Design section. Each set generated will be reviewed by a clinician involved in the study and assessed for extreme variability and overall safety. Sets that pass this screening will be saved and assigned randomly to participants at the time of the study data collection. Examples of an acceptable and unacceptable set are shown in Table 5.

**Table 5 table5:** Acceptable and unacceptable respiratory rate sets.

	First rate	Second rate	Third rate	Fourth rate	Fifth rate	Sixth rate
Acceptable	6	10	23	17	28	32
Unacceptable	5	31^a^	22	14	26	9^a^

^a^Rates with extreme variability.

Another potential risk for participants using the RespiraSense device is the risk of reaction to the adhesive. This risk has two parts. The first is allergic reaction to the adhesive. This risk has been given a risk level of 2 by the PMD risk management team. A risk level of 2 indicates the risk has been reduced as low as possible. Although the severity of this potential risk is high, this occurrence has not been observed by PMD in any use of the device and has not been found in literature searches. This risk is mitigated by excluding volunteers who are allergic to medical-grade adhesive.

The second component is a mild reaction to the adhesive. This has been given a risk level of 2 by the PMD risk management team. A risk level of 2 indicates the risk has been reduced as low as possible. This risk is of low severity (mild reaction/discomfort) and moderate occurrence level. This risk is mitigated by excluding volunteers based on a skin fragility assessment. It is also possible that mild irritation that will not require medical intervention may be experienced for patients on oral steroids.

The procedures will be carried out in the simulation suite in the Learning and Development department which is located within the Resuscitation Department of PHT, and an experienced member of the resuscitation team will always be present. If a participant should become unwell as a result of the procedures, they will be withdrawn from the study and assessed by clinical team, and subsequently care will be escalated as appropriate.

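### The fixed order (45 degrees, then one other position, then reading) confounds the position and reading contrasts with block order

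*Protocol article*

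**What the plan says.** The sequence is set out under Study Design in the protocol article.

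- First block: "Each participant will be studied in the normal position (ie, sitting at 45 degrees on a couch) for 6 different metronome rates".
- Second block: "They will then be studied in one of the three following additional positions for an additional 4 metronome rates". The three choices are supine, left lateral and sitting at 90 degrees.
- Reading: "Following the 10 metronome rates, the participant will then be asked to read a verse from a book for 2 minutes", and then "Once the participant has finished reading aloud, the study will finish".
- What varies between participants is the metronome rate: "the order of the different rates will vary with each participant to ensure the rates are random".

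The text describes no counterbalancing of position, no return to 45 degrees and no repeat baseline. Figure 1, the process flow, is not shown, but the wording above already fixes the order.

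Under Objectives, the effects of position and of reading aloud on agreement are the first two secondary objectives, both exploratory in wording. Under Statistical Analysis, the position question is answered by an analysis of variance of 45 degrees against the other positions for each pair of methods. No order or time term is mentioned. The Limitations section deals with awareness of being monitored and does not mention order.

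**The concern.** Within every participant, 45 degrees means early, the other position means late, and reading means last. Anything that changes the between-method difference over the session would be reported as an effect of position or of reading. The set-up offers possible sources: an adhesive motion sensor, a nasal cannula that can shift, and a health care professional counting epoch after epoch.

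At stake are the answers to two secondary objectives. The study could report that agreement is worse (or better) away from 45 degrees or during reading when only order is at work, or order could mask a real effect. The problem comes from the design, so an analysis plan written later can repair it only in part.

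**Working it through.** **The plan's own figures.** Tables 3 and 4 reproduce in all 29 rows. Table 3 uses N = (1.96 × SD / precision)², for example (1.96 × 1.79 / 0.25)² = 196.94, rounded up to 197. Table 4 uses three times that quantity, for example 3 × (1.96 × 1.79 / 0.4)² = 230.79, rounded up to 231. They concern primary precision and do not bear on this point. The plan gives no figure for the position contrast.

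**Inputs.**
- 30 participants × 10 rates = 300 epochs: 30 × 6 = 180 at 45 degrees and 30 × 4 = 120 elsewhere (Study Design; Patient Population Size).
- SD of differences: 1.79 breaths/min against ECG or capnography and 2.5 against manual counting (Patient Population Size).
- Timing: "Each metronome rate will be maintained for 2 minutes with 2 to 5 minutes in between for transition", plus a 20-second warm-up.
- Size of any order effect: not in the document, so a range is assumed.

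**Step 1: separation in time.** Number the epochs 1 to 11.
- Mean slot at 45 degrees: (1 + … + 6)/6 = 3.5.
- Mean slot in the other position: (7 + … + 10)/4 = 8.5.
- Reading: slot 11.

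The position gap is 5 slots. One slot lasts 0.33 + 2 + (2 to 5) = 4.33 to 7.33 minutes, so the gap is about 22 to 37 minutes, or more if longer rests are taken. A linear drift of d per slot in the between-method difference biases the position contrast by 5d, and reading against 45 degrees by (11 − 3.5)d = 7.5d.

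**Step 2: what a model could recover.** An indicator for position and an indicator for block are the same column, so a design matrix with an intercept and both has rank 2, not 3. A step at the block change is inseparable from position.

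For a linear slot term, over slots 1 to 10:
- variance of slot = 8.25
- variance of the position indicator = 0.4 × 0.6 = 0.24
- covariance = 0.4 × 8.5 − 5.5 × 0.4 = 1.2
- r² = 1.2² / (8.25 × 0.24) = 0.73
- variance inflation factor = 1/(1 − r²) = 3.67

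Such a trend can be separated, but only by assuming that it is linear across the block change, and at 3.67 times the variance.

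**Step 3: false-positive rate under an assumed order effect.** Treat epochs as independent. SE = SD × √(1/180 + 1/120), which is 0.211 at SD 1.79 and 0.295 at SD 2.5. With an order effect b between blocks and no position effect, the chance of p < 0.05 is 1 − Φ(1.96 − b/SE) + Φ(−1.96 − b/SE).

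| Assumed order effect b (breaths/min) | Equivalent drift per slot, b/5 | SD 1.79 | SD 2.5 |
|---|---|---|---|
| 0.10 | 0.02 | 8% | 6% |
| 0.25 | 0.05 | 22% | 14% |
| 0.50 | 0.10 | 66% | 40% |
| 0.75 | 0.15 | 94% | 72% |

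**Step 4: after counterbalancing.** Counting metronome epochs only, if half the participants take the other position first, the mean slot at 45 degrees is (3.5 + 7.5)/2 = 5.5 and in the other position (8.5 + 2.5)/2 = 5.5. Bias from linear drift is then zero, position and block order have full rank, and the 300 epochs are unchanged.

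**The case against.** The strongest defence is concurrency: "The different methods will be employed concurrently on the same participant as part of a single study visit". Every method sees the same breaths, so fatigue or elapsed time alone does no harm; only a change in the difference between methods does. Rests separate the rates, candidates are screened on a fast-breathing run, and the sensor is meant for continuous recording. Nothing in the document shows drift within a session. This stands: the confounding is certain, but its size is unknown, and the percentages above hold only for the assumed effects. Learning or tiring by the person counting can affect only the comparisons with manual counting, for which SD 2.5 and the lower percentages apply.

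The position and reading objectives are also secondary and exploratory. That stands too and limits the severity.

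Four stronger readings are tempting but not supported.

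- *No analysis could help.* This is strictly true only of a step at the block change. A smooth trend can be modelled under an assumption.
- *All position results are compromised.* The three additional positions occupy the same slots, so comparisons among them are not confounded with order. The primary agreement objective makes no position contrast, although its data pool both blocks.
- *Reading is confounded with posture.* Posture during reading may be set out in Figure 1, which is not shown.
- *Rate is tied to time too.* A reader might infer this from the safety screen, "the randomization of the RRs selected will be prescreened to prevent high variability between tachypnoea and bradypnea in a short space of time", and from the accepted examples in Tables 2 and 5. These are three distinct sets, and all climb (rank correlations of order with rate 0.94, 0.89 and 0.89). The inference fails. A limit on step size treats a sequence and its reverse alike, so descending sets pass as readily as ascending ones. In simulated orders with the largest step capped at 13 or 16 breaths/min (the examples fit any cap in that range), the mean absolute correlation is about 0.80 or 0.66. With its sign kept, the mean was about zero in the simulations where it was checked. Three illustrative sets do not show a common direction across 30 participants.

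**Conclusion.** The point holds for block order. As written, the 45-degrees-against-other analysis and any reading contrast cannot distinguish the condition from its place in the session, except by assuming the shape of any trend. How much this matters depends on a drift in between-method differences that the document neither reports nor rules out. An order effect of 0.10 breaths/min barely moves the nominal 5% error rate; one of 0.50 raises it to 66% at SD 1.79 or 40% at SD 2.5. Those rates treat the 300 epochs as independent and use the plan's own SDs; a within-participant analysis would change the standard errors but not the bias.

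This is a should-fix design improvement to two secondary objectives. It does not undermine the primary one, and it does not extend to the order of the rates.

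**What to change.** Before recruitment starts:

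1. Randomise which position block comes first, 15 participants each way.
2. Include block order in the position model.
3. Vary where reading falls. One option is the end of the 45-degree block, which would itself come first or second. This moves reading to slot 7 or 11 and cuts its gap from the 45-degree mean from 7.5 slots to 3.5 (7 − 3.5, or 11 − 7.5). It reduces the time confound without removing it, and leaves the positions half a slot apart: (9.5 + 2.5)/2 = 6.0 against 5.5. Placing reading before the 45-degree block for about half of each order group and after it for the rest would bring both gaps close to zero.

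The screening of rate sets stays as it is.

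The cost is a changed allocation sheet and one extra change of position for some participants, with no additional epochs or visits. The article reports that recruitment has not begun.

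If the fixed order is kept, add to the Limitations that the position and reading contrasts are confounded with order, and word their conclusions accordingly.
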